#### Data preprocessing

Prior to ML modelling, the dataset will undergo a structured preprocessing pipeline to ensure data quality and analytical robustness.

Data cleaning: Duplicate records, implausible values, and inconsistencies were identified and corrected where appropriate. Outliers were assessed using statistical and clinically informed thresholds.Missing data handling: The extent and pattern of missing data are assessed prior to analysis. Continuous variables are imputed using median, k-nearest neighbour (KNN), or multiple imputation methods, as appropriate, while categorical variables are imputed using mode-based methods. To minimize information leakage, imputation is performed using the training dataset only, with the learned imputation parameters subsequently applied to the validation dataset. No clinically implausible default values were assigned during preprocessing.Feature scaling: Continuous variables were standardized or normalized to ensure numerical stability and compatibility across ML algorithms.Categorical encoding: Categorical variables (e.g. sex, smoking status, ethnicity) were converted into numerical representations using appropriate encoding techniques.Feature engineering: Additional clinically relevant variables, including stress–response and haemodynamic indices, were be derived from existing measurements.Class imbalance handling: Outcome imbalance will be assessed and addressed using strategies such as class weighting or oversampling within the training dataset.Data partitioning: The dataset is randomly divided into development (80%), internal validation (20%) cohorts using stratified sampling to preserve event rates across all datasets. Hyperparameter optimization is restricted to the development cohort with internal validation performed exclusively within the validation dataset.

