### Stage 2: machine learning model development

The cohort is divided into training and validation sets, with 20% of the data held out for internal validation. Supervised machine learning models are developed using demographic characteristics, clinical risk factors, physiological measurements obtained during SE, and imaging-derived variables. The evaluated algorithms include ensemble methods (Random Forest and Gradient Boosting), SVM, and artificial neural networks (ANNs). Hyperparameter optimizations are performed using Bayesian optimization within nested cross-validation. Model selection is based on discrimination, calibration, robustness across validation folds, and clinical interpretability. SHapley Additive exPlanations (SHAP) is subsequently used to quantify feature importance and improve model transparency.

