#### Model development and evaluation

Selected features will then be used for prognostic modelling using approached such as logistic regression, LASSO regression (Least Absolute Shrinkage and Selection Operator), Cox survival model, and Random Forest survival model. Hyperparameters will be optimized using grid search and random search strategies. Model performance will be evaluated using accuracy, sensitivity, specificity, true positive rate, and true negative rate. A five-fold cross-validation strategy will be employed to ensure robustness and reduce sampling bias. In each iteration, models will be trained on four folds and will be evaluated on the remaining fold, with the process repeated until all folds were used for validation.

To minimize overfitting, model development incorporates a held-out validation cohort for internal performance assessment, and final model performance will be further evaluated in geographically distinct external validation cohorts with long-term clinical follow-up (including EVAREST and Stress Echo 2030, where available) to assess generalisability.

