### Statistical methods

Participant demographics and characteristics are summarized with descriptive statistics. Categorical variables are expressed as median (interquartile range), and continuous variables are expressed as mean (standard deviation). Internal model validation will be performed with 5-fold cross-validation. Cox-regression model was fitted to estimate the hazard rates, hazard ratios (HR) and the 95% CIs. Survival probabilities from any event for the first time since SE will be evaluated using Kaplan–Meier curves. Performance evaluation for the model will include measurements of Accuracy alongside Sensitivity and Specificity, using receiver Operating Characteristic (ROC) analysis with c-statistics, together with calibration plots and risk reclassification. The study will perform comparative assessments between ML models and the QRISK3 calculator to evaluate their incremental predictive value. Statistical analyses will be performed using Stata 18.0 (StataCorp LP, College Station, TX) and the R environment (R 4.5.1, The R Foundation for Statistical Computing, http://www.R-project.org) using R studio (version 2024.12.1). All tests were two-sided and α was set at 0.05, unless specified otherwise.

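### Two different procedures are named as the internal validation (20% hold-out only, and 5-fold cross-validation), and the data used for outcome-driven feature selection are not fixed

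*Protocol article*

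**What the plan says.** All places are in the Protocol article.

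- **Data preprocessing (data partitioning):** "The dataset is randomly divided into development (80%), internal validation (20%) cohorts using stratified sampling", and then "Hyperparameter optimization is restricted to the development cohort with internal validation performed exclusively within the validation dataset".
- **Stage 2: machine learning model development:** the hold-out is repeated, "with 20% of the data held out for internal validation". On tuning: "Hyperparameter optimizations are performed using Bayesian optimization within nested cross-validation".
- **Model development and evaluation:** "Selected features will then be used for prognostic modelling". A five-fold scheme follows: "In each iteration, models will be trained on four folds and will be evaluated on the remaining fold". The next paragraph gives a held-out cohort the job of assessing internal performance. On tuning: "Hyperparameters will be optimized using grid search and random search strategies".
- **Statistical methods:** "Internal model validation will be performed with 5-fold cross-validation".
- **Feature selection and ranking:** JMIM is described as a filter that scores candidates by their dependence on the outcome. This comes before the modelling and five-fold steps.

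The leakage rules in Data preprocessing confine imputation and class-imbalance resampling to the training data, and tuning to the development cohort. They do not mention feature selection. External validation in independent cohorts is planned as a later, separate step.

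**The concern.** Two procedures cannot both be the internal validation if one of them is exclusive. The article does not say whether the five-fold loop runs inside the 80% or on the whole cohort, nor which result will be reported as internal performance. An analyst could follow either sentence and be within the plan.

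The two routes give different answers. The hold-out estimate uses a fifth of the events and is imprecise. The cross-validated estimate is more precise, but it is honest only if every step that looks at the outcome is repeated inside each training fold. JMIM looks at the outcome, and nothing in the text ties it to training data. The study's purpose is to show added value over QRISK3 and over SE positivity, so a small optimistic shift, or a wide interval, bears directly on its main claim.

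**Working it through.** **1. Passages side by side**

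| Section | Internal validation | Fits cross-validation as tuning inside the 80%? |
|---|---|---|
| Data preprocessing | 20% hold-out, exclusively | Yes |
| Stage 2 | 20% hold-out | Yes |
| Model development and evaluation | Five-fold loop and a held-out cohort | Perhaps |
| Statistical methods | 5-fold cross-validation | No: it is named as the validation itself |

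The reconciling reading fails at the last row.

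**2. Size of the hold-out.** 0.20 × 2263 (Table 1) = 452.6. With the 2267 in the text it is 453.4, and with the planned 2300 it is 460. I use 453. The article states no event rate, event count or precision target for internal validation, so there is no figure of its own to reproduce here. Event rates of 3% to 30% are my assumption.

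**3. Precision of the AUC.** Hanley-McNeil, with n1 events, n0 non-events and A = 0.75 (assumed):

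SE² = [A(1−A) + (n1−1)(Q1−A²) + (n0−1)(Q2−A²)] / (n1·n0), where Q1 = A/(2−A) = 0.6 and Q2 = 2A²/(1+A) = 0.6429.

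At 5% in the hold-out, n1 = 23 and n0 = 430. SE² = (0.1875 + 22 × 0.0375 + 429 × 0.0804)/9890 = 0.00359, SE = 0.060, and the half-width is 1.96 × SE = 0.117.

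| Assumed event rate | Hold-out events (n = 453) | Hold-out half-width | All-patient events (n = 2263) | All-patient half-width |
|---|---|---|---|---|
| 3% | 14 | 0.150 | 68 | 0.068 |
| 5% | 23 | 0.117 | 113 | 0.053 |
| 10% | 45 | 0.085 | 226 | 0.038 |
| 20% | 91 | 0.062 | 453 | 0.028 |
| 30% | 136 | 0.052 | 679 | 0.023 |

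The all-patient column is approximate, because it treats pooled out-of-fold predictions as independent.

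Calibration behaves alike. Approximate 95% limits for observed/expected around 1 are exp(±1.96·√((1−p)/events)). At 5% this gives 0.67 to 1.49 in the hold-out and 0.84 to 1.20 on all patients. At 20% it gives 0.83 to 1.20 and 0.92 to 1.09.

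**4. Optimism if JMIM is run once before the folds.** Simulation with 2263 patients and 30, 60 or 100 independent candidates (assumed; the article gives no count). The top 10 were chosen by univariate correlation with the outcome as a stand-in for JMIM, followed by logistic regression with five folds, 60 replicates per setting. Selection was done either once on all data or within each training fold. The entries are the cross-validated AUC with selection outside the folds minus that with selection inside, when 8 candidates carry real signal:

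| Event rate | 30 candidates | 60 candidates | 100 candidates |
|---|---|---|---|
| 3% | 0.051 | 0.088 | 0.111 |
| 5% | 0.029 | 0.051 | 0.068 |
| 10% | 0.013 | 0.019 | 0.026 |
| 20% | 0.005 | 0.009 | 0.011 |

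With no signal at all, selection outside the folds gave an AUC of 0.54 to 0.66 where the truth is 0.50; selection inside gave 0.49 to 0.51. That is the extreme case, not the expected one.

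**The case against.** The strongest defence is that most of the text points one way. Data preprocessing, Stage 2 and the closing paragraph of Model development and evaluation all give the reported internal estimate to the hold-out. Five-fold cross-validation is introduced there for robustness, and Statistical methods is the outlier. External cohorts are the final test in any case. This narrows the ambiguity but does not remove it, because the Statistical methods sentence says the opposite without qualification. It is a contradiction in print, not a detail left to a fuller document.

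Four stronger readings are tempting and are not supported:

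- **Features are selected before the folds.** A reader might infer this from the order of the sections and from "Selected features will then be used for prognostic modelling". That is narrative order. No section says which data JMIM is run on, and nested cross-validation in Stage 2 leaves room for selection inside folds. The optimism is therefore conditional.
- **SHAP also pre-selects features.** It shares a heading with JMIM, but it is described as explaining predictions of a fitted model, and Stage 2 places it after model selection.
- **The two tuning methods contradict each other.** Bayesian optimization follows a list of random forest, boosting, SVM and neural networks. Grid and random search follow logistic, LASSO, Cox and survival forest models. They may be meant for different families; the text only fails to say so.
- **The hold-out is too small to separate the ML score from its comparators.** That would need an expected AUC difference and a correlation between the scores. The article gives neither.

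The event rate also matters. Outcomes include all-cause death and composite events over as long as 10-20 years, so rates of 20-30% are possible. There the hold-out is moderately precise and the optimism small.

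**Conclusion.** The contradiction stands: the plan names two incompatible sources for its internal performance estimate. Moving from the hold-out to out-of-fold predictions on all patients cuts the AUC half-width by a factor of about 2.2 (0.117/0.053 at 5% events). The hold-out is clearly imprecise at event rates up to about 10% and moderately precise at 20-30%. These figures rest on assumed event rates and an assumed AUC of 0.75.

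The feature-selection point stands only as an open question about which data JMIM uses. If it is run once before the folds, the simulated optimism ranges from negligible at 20% events to material at 3-5%, and depends on an assumed candidate count and a simplified filter. If it is run before the 80/20 split, the hold-out is no longer clean either. This should be settled before performance results are reported. It does not undermine the planned external validation.

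**What to change.** Name one internal-validation procedure as the source of the reported performance and of the differences between the ML score and QRISK3 and SE positivity. Repeated nested 5-fold cross-validation on all analysable patients is preferable. Imputation, scaling, resampling, JMIM and tuning are refitted within each outer training fold, with tuning in the inner loop. The final model is then refitted on all patients and carried to the external cohorts.

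Amend the conflicting sentences in Data preprocessing, Stage 2, Model development and evaluation, and Statistical methods to match. State which tuning method applies to which model family.

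If the 80/20 split is kept instead, say that the hold-out is the only reported internal estimate and that cross-validation and JMIM run only inside the 80%, and correct the Statistical methods sentence. This also resolves the conflict, at the price of the wider intervals shown above.

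The cost of the preferred option is more computing time and the loss of a single held-out figure to quote. No new data are needed.

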### Stage 2: machine learning model development

The cohort is divided into training and validation sets, with 20% of the data held out for internal validation. Supervised machine learning models are developed using demographic characteristics, clinical risk factors, physiological measurements obtained during SE, and imaging-derived variables. The evaluated algorithms include ensemble methods (Random Forest and Gradient Boosting), SVM, and artificial neural networks (ANNs). Hyperparameter optimizations are performed using Bayesian optimization within nested cross-validation. Model selection is based on discrimination, calibration, robustness across validation folds, and clinical interpretability. SHapley Additive exPlanations (SHAP) is subsequently used to quantify feature importance and improve model transparency.

#### Feature selection and ranking

Feature importance will be assessed using two complementary approaches:

**Joint mutual information maximization (JMIM)**
^
19
^: JMIM is a filter-based feature selection method that evaluates the joint dependency between candidate features and the outcome variable while accounting for redundancy among selected features. As a classifier-independent approach, JMIM is well suited for identifying informative features in high-dimensional clinical data.
**SHapley Additive exPlanations (SHAP)**
^
20
^: SHAP values will be computed to quantify the contribution of individual features to model predictions, supporting interpretability and facilitating clinical insight into model behaviour.

#### Model development and evaluation

Selected features will then be used for prognostic modelling using approached such as logistic regression, LASSO regression (Least Absolute Shrinkage and Selection Operator), Cox survival model, and Random Forest survival model. Hyperparameters will be optimized using grid search and random search strategies. Model performance will be evaluated using accuracy, sensitivity, specificity, true positive rate, and true negative rate. A five-fold cross-validation strategy will be employed to ensure robustness and reduce sampling bias. In each iteration, models will be trained on four folds and will be evaluated on the remaining fold, with the process repeated until all folds were used for validation.

To minimize overfitting, model development incorporates a held-out validation cohort for internal performance assessment, and final model performance will be further evaluated in geographically distinct external validation cohorts with long-term clinical follow-up (including EVAREST and Stress Echo 2030, where available) to assess generalisability.

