### Sample size calculation

The study aims to include approximately 2300 patients undergoing SE for the assessment of inducible myocardial ischaemia. The sample size was determined based on anticipated event rates, longitudinal outcome modelling requirements, and the complexity of the proposed ML framework.

Previous SE studies and cardiovascular outcome registries suggest that MACE are expected to occur at sufficient frequency within long-term follow-up to support robust prognostic modelling.^12^ The projected cohort size is anticipated to provide an adequate number of outcome events to satisfy event-per-variable requirements for both conventional statistical analyses and ML-based predictive modelling, while reducing the risk of model overfitting. The proposed sample size is also considered sufficient to support internal cross-validation, subgroup analyses, calibration assessment, and the evaluation of multiple supervised ML approaches, including ensemble methods, support vector machines (SVMs), and neural networks. In addition, linkage with longitudinal NHS outcome datasets over extended follow-up periods is expected to strengthen survival modelling and time-to-event prediction analyses.

External validation using independent multicentre SE cohorts is planned to further assess model generalisability and robustness across different clinical settings.

*
Table 1
* shows the characteristics of the patient population.

**Table 1 qyag143-T1:** Population characteristics

Variable	Total	Positive SE	Negative SE	*P*-value
Anthropometric variables				
*N*	2263	371 (16%)	1892 (84%)	—
Age (years)	63 (55–72)	64 (57–72)	63 (54–72)	0.031
Male Sex	1201 (53%)	243 (65%)	958 (51%)	<0.0001
Race				
Caucasian	2048 (91%)	330 (89%)	1718 (91%)	0.42
Asian	152 (7%)	27 (7%)	125 (7%)	0.85
Black	39 (2%)	8 (2%)	31 (2%)	0.71
Other	24 (1%)	6 (2%)	18 (1%)	0.31
Height (cm)	167 (160–175)	168 (160–176)	167 (160–175)	0.285
Weight (kg)	80 (68–95)	82 (70–98)	79 (67–94)	0.009
BMI (kg/m^2^)	28.7 (24.8–33.5)	29.0 (25.1–33.9)	28.6 (24.7–33.4)	0.198
BSA (m^2^)	1.90 (1.75–2.08)	1.93 (1.78–2.11)	1.89 (1.74–2.07)	0.012
Cardiovascular risk factors factors				
Hypertension	1371 (61%)	240 (65%)	1131 (60%)	0.072
Dyslipidaemia	1345 (59%)	238 (64%)	1107 (59%)	0.031
Current Smoker	218 (10%)	44 (12%)	174 (9%)	0.092
Former Smoker	648 (29%)	114 (31%)	534 (28%)	0.285
Diabetes Mellitus	671 (30%)	127 (34%)	544 (29%)	0.036
Obesity (BMI ≥30)	232 (10%)	30 (8%)	202 (11%)	0.142

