### Expected outcomes

Development of a robust ML-based predictive model for adverse outcomes in SE. Identification of significant predictors, including echocardiographic, clinical, and demographic variables. Demonstration of the incremental value of ML over traditional statistical methods in improving diagnostic accuracy and risk stratification (*Figure 2*). Insight into the feasibility of integrating ML models into clinical workflows to personalize patient care and optimize resource utilization. (*Figure 2*).

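### Features selected on the outcome go on to Cox hazard ratios with ordinary 95% CIs at 0.05; if the same patients serve both steps, those CIs are too narrow and significance claims for selected predictors are unreliable

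*Protocol article*

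**What the plan says.** The relevant statements stand in five places in the protocol article.

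- **Feature selection and ranking (JMIM).** The filter "evaluates the joint dependency between candidate features and the outcome variable", so selection is driven by the outcome.
- **Model development and evaluation.** "Selected features will then be used for prognostic modelling using approached such as logistic regression, LASSO regression"; the same sentence goes on to name a Cox model and a random survival forest. This is the only Cox model in the article whose inputs are described.
- **Statistical methods.** "Cox-regression model was fitted to estimate the hazard rates, hazard ratios (HR) and the 95% CIs", followed by the general rule "All tests were two-sided and α was set at 0.05, unless specified otherwise". No allowance for selection is mentioned.
- **Expected outcomes.** "Identification of significant predictors, including echocardiographic, clinical, and demographic variables".
- **Data preprocessing.** "The dataset is randomly divided into development (80%), internal validation (20%) cohorts", and "Hyperparameter optimization is restricted to the development cohort". Imputation is likewise learned on the training data. Neither feature selection nor HR estimation is assigned to a cohort.

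The hold-out and the external cohorts are given the task of assessing model performance. They are not given the task of estimating or confirming individual coefficients.

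**The concern.** An ordinary Wald interval for a Cox coefficient assumes that the covariate was named without looking at the outcome. A feature that entered because it looked associated with the outcome in the same patients has already passed a test on those data. Its interval is then too narrow, and its HR tends to be exaggerated.

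This differs from optimism in the AUC. Placing selection inside the cross-validation folds, or measuring performance in the hold-out, corrects the performance estimate. It does nothing for the HRs, CIs and p-values of the selected features.

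At stake is the list of echocardiographic, clinical and demographic predictors that the article names as an output. That list could include noise variables with CIs excluding 1, and the HRs of borderline true predictors could be overstated.

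**Working it through.** **Inputs from the article.** Two-sided alpha 0.05. Table 1 has 2263 patients, split 80/20: 0.8 × 2263 ≈ 1810 and 0.2 × 2263 ≈ 453.

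**Inputs assumed.** The article gives no event rate, no number of candidate features and no number kept. Assumed: 20% of patients with an event; 30, 40 or 60 independent candidates; 5 to 20 kept; either no true predictors or 5 with log HR 0.25.

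**Step 1, benchmark.** The only stated figure is alpha. Suppose p independent noise candidates are ranked by their own test statistic and the k strongest are kept. The share of kept features with p<0.05 is

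E[min(k, X)] / k, with X ~ Binomial(p, 0.05).

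With no selection (k = p) this returns 0.05, the stated level.

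**Step 2, selection and testing on the same data, analytic.** For p = 40, E[X] = 40 × 0.05 = 2.

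- keep 20: 2/20 = 10.0%
- keep 15: 2/15 = 13.3%
- keep 10: 2/10 = 20.0%
- keep 5: 1.98/5 = 39.6% (the cap at 5 binds slightly)

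These are values for a filter that ranks by the test statistic itself. JMIM ranks by a different measure, so it was simulated.

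**Step 3, simulation with JMIM.** Features were binned in tertiles and selected on the 80%. A multivariable Cox model with Wald tests was fitted on the same 80% and, separately, on the untouched 20%, with 100 runs per row. The percentages in the third and fourth columns are shares of selected noise features with p<0.05.

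| Candidates (true predictors) | Kept | Same 80% | Untouched 20% | Per noise candidate entered, same 80% |
|---|---|---|---|---|
| 30 (0) | 10 | 14.5% | 6.7% | 4.8% |
| 40 (0) | 10 | 15.6% | 6.3% | 3.9% |
| 40 (0) | 5 | 20.8% | 4.4% | 2.6% |
| 40 (5) | 10 | 18.0% | 5.3% | 2.6% |
| 40 (5) | 15 | 12.7% | 5.2% | 3.7% |
| 60 (5) | 10 | 24.0% | 5.8% | 2.3% |
| 30 (5) | 20 | 6.9% | 5.5% | 4.1% |

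The same-data range is 6.9/5 = 1.4 to 24.0/5 = 4.8 times nominal. It shrinks as more of the candidates are kept.

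In the untouched 20% the rate is close to 5%. The highest value, 6.7%, comes from about 1000 tests (standard error √(0.05 × 0.95/1000) = 0.7 points). Any small excess there cannot come from selection, because those patients took no part in it.

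**Step 4, correlation.** The rows above use independent features, whereas the study's features are plainly related (WMSI, blood pressure and heart rate by stage; weight, BMI and BSA). In a second simulation with JMIM on quintile bins, a pairwise correlation of 0.3 gave about 5%, so no excess. With 45 candidates in blocks of five (60 runs), the rate was 7% to 12% at within-block correlation 0.5 and 19% at 0.8. The direction of the problem is clear, but its size depends on inputs that the article does not give.

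**The case against.** The strongest reply is that the article never states the error outright. The sentence on Cox HRs names neither covariates nor the patients used. Stage 3 compares the ML score with QRISK3 and SE positivity, so that Cox model could concern these pre-named exposures. The Stage 2 models are judged by accuracy, sensitivity and specificity, importance is described through JMIM and SHAP, and the word significant may be meant loosely. Which cohort supplies the HRs is a detail that an analysis plan may settle.

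Much of this stands, and it is why the point is conditional. It does not remove the point. The article does state outcome-based selection, the passing of selected features into a Cox model, Cox HRs with CIs under a general 0.05, and significant predictors as a product. Its validation data are assigned to performance only.

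A reader might infer more than the documents support:

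- **That the list is bound to contain noise at several times 5%.** The size rests on unstated inputs and can fall to nominal with correlated features.
- **That every candidate faces an inflated error rate.** Per noise candidate entered, the JMIM rate was 2.3% to 4.8%. The excess applies to noise features that survive selection, although those are the ones that would be reported.
- **That the excess reaches tenfold.** A simple correlation filter gave 7.8% to 50.1% in the same settings, but the article does not plan that selector. LASSO is listed beside Cox, not as a step before it, and was not simulated.
- **That the prediction results are compromised.** They are judged in held-out and external cohorts, and this point leaves them untouched.

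**Conclusion.** The point holds in conditional form. If selection and HR estimation share patients, as the Stage 2 sequence implies, ordinary CIs and a 0.05 threshold are not valid for the selected features, and their HRs will tend to be exaggerated.

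For JMIM with 30 to 60 independent candidates, 5 to 20 kept and 20% events, about 7% to 24% of selected noise features reach p<0.05 against a nominal 5%. All of these inputs are assumptions. The consequence is confined to the HRs, CIs and significance claims for selected predictors. Discrimination, calibration and reclassification in validation data are not affected.

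**What to change.** 1. In Model development and evaluation and in Statistical methods, state that HRs of outcome-selected features estimated in the data used for selection are descriptive, without p-values or significance claims. Alternatively, take their CIs from a bootstrap that repeats the whole selection step in each resample.
2. Limit inferential HRs at 0.05 to covariates fixed in advance without reference to the outcome, for example QRISK3 and SE positivity (the base models of Stage 3), or to confirmation in the external cohorts.
3. Treat HRs from the 20% hold-out as supportive only. At the assumed 20% event rate it holds about 453 × 0.20 ≈ 91 events, or roughly 9 to 4.5 per variable for 10 to 20 features. Its CIs would be about √(1810/453) ≈ 2 times as wide as those from the development set.
4. In Expected outcomes, replace the reference to significant predictors with *candidate predictors, confirmed where possible in data not used for selection*.

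The cost is wording, plus computing time if the bootstrap is chosen. The downside is that fewer predictors can be called significant.
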